**Abstract**

Approximately 1 million children < 5 y living in sub-Saharan Africa die from severe anemia annually. This severe anemia frequently results from coexisting iron deficiency and malaria infection, but the standard of care, concurrent iron therapy and antimalarial treatment, has proven ineffective at curing the profound anemia and has promoted proliferation of the parasite in some studies. The pro-inflammatory immune response mounted against malaria down-regulates iron absorption in the gut, making provision of oral iron supplements during malarial infection of questionable utility. The present study uses iron stable isotopes and a randomized design to test whether starting 4 weeks of iron therapy immediately after antimalarial treatment or 4 weeks later is associated with greater iron incorporation into red blood cells at the time of initial administration of iron therapy and improved long-term hematological recovery. One hundred Ugandan children 6-59 mos with anemia (hemoglobin 5-9.9 g/dL) and with clinical signs of malaria who present to the Pediatric Acute Care Ward of Mulago Hospital in Kampala, Uganda, will be randomized to start iron immediately after antimalarial treatment on Day 0 (immediate group) or 4 weeks later on Day 28 (delayed group). Children will be assessed at the hospital on Day 0, Day 28 and Day 56 and will receive bi-weekly home visits for the 56-day study duration. The specific aims and corresponding hypotheses of the proposed study are:

**Aim 1: Identify the sequencing of antimalarial treatment and iron therapy that results in the greatest red cell iron incorporation at the time of initial iron supplement administration.** The working hypothesis is that red cell iron incorporation will be greater at the time of initial supplement administration in children starting iron 4 weeks after antimalarial treatment (delayed group) compared to children starting iron concurrently with antimalarial treatment (immediate group), due to more complete parasite clearance and resolution of inflammation, permitting better iron uptake, distribution, and utilization.

**Aim 2: Determine whether long-term hematological recovery is impacted by immediate vs. delayed iron.** The working hypothesis is that delayed iron treatment will be associated with greater hemoglobin and improved iron status at Day 56 compared to immediate treatment due to more complete parasite clearance and consequent improved iron absorption and use in the delayed group.

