| Outcomes | Aim 1: Primary outcome: Percentage of red cell iron incorporation at the time of initial iron supplement administration (Day 0 incorporation immediate group vs. Day 28 incorporation delayed group)  Secondary outcomes: Association between change in plasma iron and inflammatory indicators (EP, ferritin, sTFR, hepcidin, reticulocytes, CRP, AGP; all continuous) and change in percentage red cell iron incorporation in each treatment group between Day 0 and Day 28.  Aim 2: Primary outcomes: Change in hemoglobin from Day 0 to Day 56 in immediate vs. delayed groups.  **Secondary outcomes:** Change in iron markers (EP, ferritin, sTFR, hepcidin) from Day 0 to Day 56 in immediate vs. delayed groups. |

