The pathophysiology of anemia resulting from co-existing iron deficiency and malaria infection supports this conclusion.The anemia of malaria is complex, with hemolysis of parasitized red blood cells, clearance of both parasitized and non-parasitized red blood cells by reticulo-endothelial macrophages, and impaired bone marrow activity all contributing.^12,13^ Iron that would normally be recycled from degraded red blood cells and transported to the bone marrow for erythropoiesis is instead sequestered in reticulo-endothelial stores under the influence pro-inflammatory cytokines IL-1, IL-6, TNF-α, IFN-γ, the same cytokines implicated in contributing to the alterations in iron metabolism characteristic of the anemia of chronic disease.^14-17^ The antimicrobial hepatic protein hepcidin, an integral regulator of iron metabolism that serves as the soluble messenger among the sites of iron absorption, erythropoiesis, and storage,^18^also plays a key role in these inflammatory changes. Hepcidin concentrations rise during iron sufficiency, down-regulating intestinal iron absorption, and fall during iron deficiency, up-regulating iron absorption. Hepcidin is also a positive acute phase response protein whose concentrations are up-regulated during inflammation under the influence of IL-6^19^--a finding that is thought to explain the alterations of iron metabolism (hypoferremia, hyperferritinemia, anemia) during infectious and non-infectious inflammatory states. Hepcidin acts primarily by binding and degrading the iron-exporting protein ferroportin,^20,21^ blocking iron efflux from intestinal and reticulo-endothelial cells. Multiple studies have confirmed that hepcidin concentrations increase with *P. falciparum* infection^7, 22,23^ and that even mild increases in serum hepcidin can lead to profound disturbances in iron metabolism, including marked hypoferremia, increased serum ferritin, and reduced incorporation of hemoglobin into reticulocytes.^7^

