These changes appear to be resolved approximately four weeks after successful antimalarial treatment. One recent study of *P. falciparum*-infected, hospitalized Tanzanian children aged 2 mo-13 y who were anemic and febrile found that urinary concentrations of hepcidin at baseline were high and were associated with hypoferremia and increased serum ferritin.^7^ Antimalarial treatment rapidly decreased hepcidin concentrations and reversed hypoferremia. Serum iron concentrations and transferrin saturation rose rapidly, but significant changes in total iron binding capacity and serum ferritin were observed only after four weeks. Concentrations of CRP and pro-inflammatory cytokines IL-1Ra and IL-6 paralleled the changes in hepcidin, falling significantly two days after antimalarial treatment and declining even further by Week 4. The authors concluded that marrow suppression in patients with febrile malaria is rapidly reversible with efficacious antimalarial treatment and that iron therapy might only be effective once hepcidin concentrations decline. A study of red cell iron incorporation in young Gambian children treated for uncomplicated malaria and given a 30-day course of iron similarly demonstrated that iron therapy might be most efficacious if given 2-4 weeks after antimalarial treatment.^8^Using iron stable isotopes, researchers found that children recovering from malarial anemia exhibited significantly lower red cell iron incorporation at baseline and at Day 15 (baseline: 8% vs. 28%, p<0.001; Day 1: 14% vs. 26%, p=0.04), but had a greater hemoglobin concentration on Day 15 and Day 30 than children with iron deficiency anemia alone, leading researchers to conclude that children in the post-malaria group met their immediate iron needs for erythropoiesis with recycled iron liberated from reticulo-endothelial stores after antimalarial treatment rather than from the oral supplement. Whether this hemoglobin recovery would have been even greater if the iron therapy had been delayed until red cell iron incorporation was more optimal, i.e., some time after Day 15, is unknown. Also unknown is whether iron absorption and subsequent incorporation into red cells would follow similar patterns in children with severe anemia and clinical malaria in whom inflammation-induced iron trapping and subsequent hypoferremia is likely more profound. To date, red cell iron incorporation during malaria infection has only been investigated in two populations, Gambian children with uncomplicated malaria, as described, and young Beninese women of childbearing-age with subclinical malaria.^24^

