**Sample collection:** *Phlebotomy:* A venous blood sample of no more than 5 mL is routinely drawn from patients with this clinical presentation as part of standard of care. Whole blood will be used for assessment of EP and reticulocytes. This Day 0 blood, along with blood samples drawn at the Day 28 and Day 56 hospital visits will be centrifuged, and plasma collected at the CoreLab located onsite at Mulago Hospital. Plasma will be stored at -80^o^C and then shipped on liquid nitrogen to the University of Minnesota for quantification of iron and inflammatory markers (ferritin, sTfR, hepcidin, CRP, AGP) by immunoassay in the lab of [name]. A finger-prick blood sample will also be drawn on Days 28 and Day 56 for hemoglobin assessment by HemoCue and for Giemsa stain preparation. Red blood cell pellets collected at Day 28 and Day 56 will be re-suspended in saline, stored at -80^o^C, and shipped to Baylor College of Medicine for isotopic analysis by inductively coupled plasma mass spectrometry (ICP-MS) in the laboratory of [name].

*Stool sample:* Per Mulago Hospital guidelines, a stool sample will be collected from each child on Day 0 and analyzed for helminths. Any child found to be infected will be treated with mebendazole.

**Statistical analysis:** For our primary outcome for Aim 1,we will compare Day 0 red cell iron incorporation in the immediate group with Day 28 red cell iron incorporation in the delayed group using a two-sample t-test. Secondary analyses will adjust for baseline characteristics of the children, including age, sex, height, and weight. For our secondary outcome of the association of the change in plasma iron and inflammatory indicators with the change in percentage red cell iron incorporation in each treatment group, strength of trends will be assessed by Spearman correlations. We will also compare the mean change in red cell iron incorporation from Day 0 to Day 28 in the immediate vs. delayed groups using separate multivariate regression models for each indicator. In each model, the change in red cell incorporation will be the outcome variable, and treatment group, Day 0 hemoglobin, and the mean changes from Day 0 to Day 28 in ferritin, sTfR, EP, hepcidin, AGP, or CRP as predictor variables. Models will be further adjusted for sex, age, and anthropometric indices.

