**Table 1: Power and sample size for Aim 1**

|  | Detectable difference | |
| --- | --- | --- |
| n per group | Power 80% | Power 90% |
| 30 | 5.2 | 6.0 |
| 33 | 5.0 | 5.8 |
| 40 | 4.5 | 5.2 |
| 43 | 4.3 | 5.0 |
| 50 | 4.0 | 4.6 |
|  |  |  |

For our primary outcome for Aim 2 of the change in hemoglobin from Day 0 to Day 56 in the immediate vs. delayed iron groups, we will compare mean 56-day change (Day 56 minus Day 0) in hemoglobin between the treatment groups using a two-sample t-test. Secondary analyses will adjust for baseline characteristics of children, including age, sex, anthropometric indices, and stool helminth count. For our secondary outcome of changes in iron indicators between Day 0 and Day 58, we will compare the mean 56-day change in each iron indicator (EP, ferritin, sTfR, hepcidin) between treatment groups using a two-sample t-test for each indicator. Secondary analyses will adjust for age, sex, anthropometric indices and helminth count.

**Sample size calculations:** Assuming a SD in the mean change in hemoglobin to be 1.5 g/dL and alpha = 0.05, with 50 children in each treatment group, we would have 90% power to detect a difference of 1.10 g/dL in the mean 56-day change in hemoglobin concentration between groups, assuming 20% loss to follow-up.

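### Aim 2 tests 56-day change in ferritin and hepcidin without using the measured CRP and AGP, which costs precision and leaves any difference open to a Day 56 inflammation explanation

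*Protocol*

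**What the plan says.** The Outcomes row of the Protocol Overview defines the Aim 2 secondary outcome as "Change in iron markers (EP, ferritin, sTFR, hepcidin) from Day 0 to Day 56 in immediate vs. delayed groups". The analysis text after Table 1 fixes the method: "we will compare the mean 56-day change in each iron indicator (EP, ferritin, sTfR, hepcidin) between treatment groups using a two-sample t-test". It then gives a covariate list: "Secondary analyses will adjust for age, sex, anthropometric indices and helminth count". CRP and AGP are not on it.

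Both are nevertheless available. The sample collection section describes "quantification of iron and inflammatory markers (ferritin, sTfR, hepcidin, CRP, AGP) by immunoassay" for plasma from Days 0, 28 and 56. Their one stated use as model terms is in Aim 1, where Day 0 to Day 28 changes in them are predictors of change in red cell iron incorporation.

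The Background sets out why this matters. On hepcidin: "Hepcidin is also a positive acute phase response protein whose concentrations are up-regulated during inflammation". It also says that hepcidin rises with iron sufficiency. From a cited study of febrile, infected children: "urinary concentrations of hepcidin at baseline were high and were associated with hypoferremia and increased serum ferritin". In that study treatment lowered hepcidin quickly, and ferritin changed significantly only after four weeks. The Abstract reads the Aim 2 markers as iron status: "delayed iron treatment will be associated with greater hemoglobin and improved iron status at Day 56 compared to immediate treatment".

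**The concern.** Ferritin and hepcidin respond to two things that the trial wants to separate: the child's iron and the child's inflammation. Every child enters with smear-positive malaria and recent fever, so the Day 0 value carries a large and variable inflammatory component by the protocol's own account. A change score carries all of it into the outcome.

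Day 56 raises a different question. If one arm has more infection or inflammation at that visit, its ferritin and hepcidin will be higher whatever its iron stores. The planned analysis could then show a difference that looks like better iron status, or miss a real one. The data needed to examine this are already collected, and the stated covariate list leaves them out.

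**Working it through.** **The plan's own figure.** The only Aim 2 power statement concerns hemoglobin: SD 1.5 g/dL, difference 1.10 g/dL, 50 per group, 20% loss, hence 40 evaluable per group.
- Normal approximation, two-sided 0.05: 1.10 / (1.5 × √(2/40)) = 3.28; 3.28 − 1.96 = 1.32; power 0.907.
- Exact t-test: power 0.900, detectable difference 1.10.

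The stated 90% reproduces, and nothing below changes it. The protocol gives no SD for ferritin or hepcidin, so all that follows is illustration under assumptions.

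**Noise from inflammation.** With 40 per group, 80% power needs (1.960 + 0.842) × √(2/40) = 0.626 SD. Let R² be the share of the variance of change that is due to inflammation (assumed). An effect with 80% power after full correction has this power uncorrected (effect multiplied by √(1 − R²)):

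| R² | 0.1 | 0.2 | 0.3 | 0.4 | 0.5 | 0.6 |
|---|---|---|---|---|---|---|
| Power | 76% | 71% | 65% | 58% | 51% | 43% |

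**A simulated example.** Assumed: log marker = stores + 0.5 × inflammation; inflammation mean 2, SD 1 on Day 0 and mean 0, SD 0.5 on Day 56; stores SD 0.6 on Day 0, rising by 0.5 with SD 0.4; 40 per group; 4,000 runs. Variance of change = 0.16 + 0.25 × 1 + 0.25 × 0.25 = 0.4725, of which inflammation is 0.3125 (66%). This is therefore a strong-inflammation case, beyond the table. Full correction assumes that the true coefficient is known, so its results are a ceiling.

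1. *No difference in stores or in Day 56 inflammation.* The t-test on change rejects in 4.8% of runs. The comparison is valid despite Day 0 inflammation, although the pooled mean change is −0.50 while stores rose by 0.50.
2. *True store difference 0.25, equal Day 56 inflammation.* The estimate is 0.25 (unbiased). Power is 37% on raw change and 79% fully corrected. ANCOVA on the Day 0 marker and Day 0 inflammation leaves residual variance 0.16 + 0.0625 = 0.2225, SD 0.472; 0.25 / (0.472 × √(2/40)) − 1.96 = 0.41, power about 66% (64% by simulation). Baseline covariates alone recover most of the loss.
3. *Equal stores, one arm 0.5 units more inflamed on Day 56.* A difference of 0.25 appears that is not stores. The t-test on change rejects in 35% of runs. ANCOVA on Day 0 values rejects in 63%, because it is more precise and does not address Day 56 inflammation. Same-visit correction returns 0.00.
4. *Arm with 0.25 more stores is 0.5 units less inflamed on Day 56.* The estimate is 0.00 by either uncorrected method.

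**Size on the ferritin scale.** If inflammation multiplies ferritin by k and the share inflamed on Day 56 differs by Δ, the ratio of geometric means at equal stores is k^Δ. The k and Δ values are all assumed.
- Δ = 0.15: 1.5^0.15 = 1.06; 3^0.15 = 1.18.
- Δ = 0.05: 1.5^0.05 = 1.02; 3^0.05 = 1.06.

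**Is a Day 56 difference plausible?** The study design row has the delayed arm taking iron from Day 29 and the immediate arm from Day 1, each for four weeks, so only the delayed arm is on iron over Days 29-56. The Background cites non-significant increases in malaria indices with iron, and the risk section names more malaria episodes as the main risk of iron therapy. Against this, the Background expects inflammatory changes to resolve about four weeks after treatment, and Day 56 is eight weeks after.

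**The case against.** The strongest reply is that the test compares randomised arms. Day 0 inflammation is balanced on average, so the point that change mostly tracks recovery from malaria describes within-arm change and not the contrast. This stands: case 1 above shows the correct error rate. A reader might infer that the febrile baseline biases the result, and it does not.

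A reader might also infer that the hypothesis itself predicts opposing effects on ferritin, with less inflammation lowering it and more iron raising it. The text does not go that far. It places the resolution of inflammation at the first iron dose and describes one chain from clearance to better absorption. It does not predict a less inflamed delayed arm on Day 56.

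The size is also open to challenge. At the worst assumed case the spurious log difference is ln 1.18 = 0.17. If the SD of log change were 0.8 to 1.2 (assumption), that is 0.14 to 0.21 SD, well below the detectable 0.63 SD. This stands too: no passage supports the 6-18% range as an expected bias.

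Finally, log transformation and assay correction are often left to an SAP, and Day 56 CRP and AGP are post-randomisation. The first part is fair for transformation. It does not cover the covariate list, which the protocol states. The second part limits the remedy but does not remove the need for one.

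**Conclusion.** The point holds for two secondary markers. The protocol fixes an analysis of ferritin and hepcidin that leaves out inflammation measures it collects and whose relevance it explains. Two consequences follow. Precision is lost: under the assumed R² of 0.1 to 0.6, power falls from 80% to between 76% and 43%. Attribution is also weakened: a difference between arms cannot be assigned to iron stores if inflammation differs on Day 56, which the dosing schedule and cited literature make possible but do not establish.

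The documents do not support a claim that Aim 2 becomes unreadable. Hemoglobin is the primary outcome. EP, which defines iron deficiency in this trial, and sTfR are also compared, and the protocol does not make the same inflammation argument for them. All sizes given here rest on assumed values, since no ferritin or hepcidin variance is stated.

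**What to change.** Keep the randomised comparison, but analyse log ferritin and log hepcidin on Day 56 by ANCOVA, adding the Day 0 marker value and Day 0 CRP and AGP to the covariates. These are pre-treatment variables, so the adjustment gains precision without conditioning on anything that treatment could affect.

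Beside it, prespecify a supportive analysis with ferritin corrected for CRP and AGP from the same visit, and show both results together. It is needed because the ANCOVA does not deal with Day 56 inflammation (case 3). It should stay supportive because Day 56 CRP and AGP may lie on the causal path from iron timing, so correcting for them can remove part of a real effect. For the same reason, restricting to children with normal Day 56 values should not replace the randomised comparison.

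Interpret hepcidin alongside CRP and AGP as a mechanistic marker, not as stand-alone evidence of improved iron status.

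The cost is analysis wording only. No samples, assays or participants are added, and the stated sample size does not change.

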**Protection Of Human Subjects**

**Proposed involvement of human subjects:** This study proposes to use iron stable isotopes to study the effect of immediate vs. 4-week delayed iron therapy to treat iron-deficiency in 100 moderately to severely anemic Ugandan children with malaria who present at the Pediatric Acute Care Unit at Mulago Hospital in Kampala, Uganda. All children will be treated for malaria according to national guidelines and then randomized to receive a 4-week course of iron therapy that starts concurrently with antimalarial treatment (immediate group) or 4 weeks after antimalarial treatment on Day 28 (delayed group). Children in both groups will receive 57Fe at baseline and 58Fe at 28 days follow-up. Proposed blood draws will be at baseline (as part of routine hospital admission), Day 28, and Day 56. This design will permit comparison of percent of iron incorporated into red cells at the time of initial supplement administration in the immediate vs. delayed groups (Aim 1) and also long-term hematological recovery between the two treatment groups (Aim 2).

**Characteristics of the subject population:** Moderate to severe anemia resulting from iron deficiency and malaria infection disproportionately afflicts very young children in sub-Saharan Africa and is a primary cause of hospitalization and mortality. Neither iron deficiency nor malaria is common in very young infants until 6 months of age, when conferred immunity from malaria via maternal antibodies wanes and birth iron stores are depleted. The rapid growth of children between 6-59 months, coupled with diets deficient in absorbable iron, places them at high risk of iron deficiency. This period of growth corresponds with peak vulnerability to malaria infection before immunity to the parasite is achieved. We proposed to enroll 100 participants, as this number provides sufficient statistical power to observe a clinically meaningful difference in red cell iron incorporation in the immediate vs. delayed groups.

**Sampling plan:** We will recruit a consecutive sample of children 6-59 months with anemia (hemoglobin 5-9.9 g/dL) and malaria. This is a group of children that commonly presents to the Pediatric Acute Care Unit at Mulago Hospital. All participants will receive extensive follow-up, including bi-weekly home visits and transportation to the hospital for scheduled visits and for any intervening illness. Within this group of moderately to severely anemic children, no distinction will made based on gender or minority. We will exclude children who live far enough from the hospital that complete follow-up would be difficult; children with hemoglobin < 5 g/dL, as these children receive transfusion upon admission; children who are not anemic (hemoglobin ≥ 10 g/dL), as our project focuses on iron absorption and utilization in anemia; and children with signs of cerebral malaria, including impaired consciousness or recent seizure activity.

**Involvement of special classes of subject:** We will be enrolling anemic Ugandan children aged 6-59 months, as the public health problem of coexisting iron deficiency and malaria infection is greatest at this age and in this part of the world.

**Study group assignment:** All children who are found to be iron-deficient (elevated erythrocyte protoporphyrin) will be randomized to receive iron concurrently with antimalarial treatment, which is the current standard of care, or 4-weeks after anti-malarial treatment. We hypothesize that children receiving delayed iron will exhibit greater long-term hematologic recovery and iron status due to more complete parasite clearance and resolution of inflammation at the time of initial supplement administrations, despite the delayed administration of iron.

All children will receive a single dose of iron stable isotope 57Fe (4 mg) at baseline and 58Fe (1.5 mg) at Day 28. Stable isotopes are a safe and accessible way to measure mineral metabolism. They are used regularly to investigate iron absorption in many vulnerable groups, including premature infants and pregnant women. The 4-week course of iron given to all iron-deficient children will be in the form of liquid ferrous sulphate, at a dose of 2 mg iron per kg body weight, as recommended by the World Health Organization.

**Collaborating sites:** This study will take place at Mulago Hospital in Kampala, Uganda. Mulago is the largest referral hospital in Uganda, and our group has collaborated with pediatric malaria researchers there for more than a decade. For the current study, on-site collaborators will be responsible for patient enrollment and care while in the hospital, administration of study interventions, obtaining and proper care of study samples, and coordination of follow-up for the duration of the study period. Our on-site data team will ensure complete data entry from clinical forms, collected in the hospital and in the field, and will conduct periodic quality checks on data integrity and completeness. All study forms will be kept in a locked desk in the Cerebral Malaria Team office, and the study database will be password-protected.

**Description of research material obtained**: Blood samples will be collected from all enrolled children at baseline, at Day 28, and at Day 56. From these blood samples, plasma will be collected, frozen, and shipped to the US for analysis of iron markers. The red blood cell pellet from each blood sample will be suspended in saline, frozen, and also shipped to the US for analysis of isotope ratios. Data from clinical forms will be kept in a password-protected database, which is routinely backed up. Paper copies of forms will be kept in a locked office. Any shared data set will be stripped of all patient identifiers.

**Description of data:** We expect to collect data on the concentrations of iron and inflammatory markers in the plasma of all enrolled children at 3 time points. We also expect to gain values of red cell iron incorporation at Day 0 and Day 28. We will further have morbidity data for the 56-day duration of the study, including the number of malaria episodes and fevers.

**Linkages and access to subject identities:** The study coordinator, home visitors, nurses, and data manager will have access to identifiable information, as it is necessary to ensure full follow-up, patient care, and accurate data entry and storage.

**Collection of specimens, records, or data:** Each participant will be given a unique study id upon enrollment. These id’s will be randomly generated, as described in the Randomization section. Upon collection, all specimens, records, and forms for each participant will be marked and linked with this unique study id. Only the study coordinator, home visitors, nurses, and data manager will be able to link study id with identifiable information, as this linkage is critical for optimal patient care while at the hospital and for complete home follow-up.

